### Analysis of secondary outcome measures

Additional analyses of clinical outcomes will include the number of days spent in intensive care; the presence and severity of mucositis and length of time requiring parenteral nutrition; days of fever post-HCT corrected for length of admission; days of antibiotics including carbapenem; the number and length of bloodstream infections; colonisation with multidrug-resistant bacteria, including extended-spectrum β-lactamases, vancomycin-resistant *Enterococci* and carbapenemase-producing *Enterobacteriaceae* and incidence of GvHD and relapse incidence. Neutrophil and platelet engraftment data, recovery of T-cell chimerism, haematological outcomes (non-relapsed mortality, occurrence GvHD and severity of GvHD).

Analysis will be completed via presentation of descriptive statistics or summary tables. Continuous outcomes will be assessed via the same mixed-model approach as per primary estimand. Frequency outcomes will use a negative binomial approach, adjusting for the same covariates as the primary estimand analysis model. In the event where data fails to satisfy model assumptions and transformation is not suitable, an appropriate non-parametric approach may be used in replacement.

Full details of analysis methodology are to be provided in the SAP.

### Safety analysis

Additional safety outcomes—including AEs, ARs (adverse reactions), SAE and SUSARs (suspected unexpected serious adverse reactions)—will be reported as frequencies, unadjusted participant proportions and/or rates where appropriate. Differences between arms with 95% CIs using exact methods will be produced where appropriate.

## Discussion

The increasing recognition of the contribution of the gut microbiome in patients with haematological malignancies undergoing cellular therapies, coupled with emergent data supporting IMT as a strategy to alter the microbiome, necessitates robust placebo-controlled IMT trials. Primarily, phase IIa trials such as MAST aim to fully evaluate the specific contribution that IMTs may have as part of patient treatment, and provide the launchpad for future phase III trials. We hope that associated microbiome, metabolomic and immune analyses will improve understanding of the mechanistic contribution of the gut microbiome to the clinical outcomes seen, potentially setting the stage for future novel targeted ‘microbiome therapeutics’ that avoid the drawbacks associated with IMT. While we envisage that most of our analyses will involve comparison of the dynamics of clinical and biological variables between the IMT and placebo arms, there may also be within-group exploratory analyses which provide further relevant insight as well (eg, comparison of ‘responders’ and ‘non-responders’ to FMT within the treatment arm only, looking for the impact of baseline host gut microbiome diversity and/or specific taxonomic features on the likelihood of response).

A growing body of non-randomised studies has described positive clinical signals when IMT was used in patients with haematological malignancies undergoing HCT.^8^ However, it was also noteworthy that a recent phase II randomised double-blind placebo-controlled trial,^23^ administering capsulised IMT or placebo after HCT for AML, timing this for after neutrophil recovery, failed to achieve its primary outcome, showing no statistical difference in the infection rate by 4 months post-HCT in the IMT arm compared with placebo. One fundamental difference in design between that study and our study is that in our trial, the IMT is targeted at the pre-HCT (rather than post-) HCT period. There were several reasons for us considering that this aspect of timing is particularly important, a factor that has also been introduced elsewhere.^24^ Most importantly, the published data related to the dynamics of the gut microbiome with HCT particularly demonstrate the close association between reduced gut microbiome diversity pre-HCT and future morbidity and mortality, as well as the emergence of *Enterococcus* domination within the gut microbiome within 3 weeks postallogeneic HCT as influencing poor outcome.^6 7^ Additionally, aberrant intestinal microbiome diversity is known to be associated with increased inflammatory response^25^ and biomarkers of inflammation measured pre-HCT were shown to be independent predictors of HCT outcomes.^26^

Therefore, we concluded that the clearest window for intervention is pre-HCT, aiming to increase the pre-HCT gut microbiota diversity, and mitigate the risk of pathobiont overgrowth is prior to start of HCT conditioning (figure 2). The concept of targeting IMT prior to intervention has also been used successfully in oncology, with a phase I study evaluating IMT use prior to immune checkpoint inhibition in 20 patients with advanced melanoma demonstrating an objective response rate of 65% (n=13/20; including 4/20 complete responses).^27^

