### Statistical considerations

#### Sample size and powering

Currently published data on alpha diversity change in patients undergoing HCT and/or IMT span different study types, vary in quality/granularity, and use different alpha diversity indices. The evidence available suggests larger decreases in alpha diversity at approximately 1-month post-HCT compared with baseline in patients who do not receive IMT relative to those that do.^2 6 8 18 19^ Fitting a mixed-effects model (with fixed effects for arm, time (day), their corresponding interaction and a random per-patient intercept effect) with quadratic splines at 5 df (3 internal knots) to longitudinal change in alpha diversity data (measured with inverse Simpson’s index) from baseline,^2^ IMT patients had an expected change in baseline alpha diversity at day 28 post-HCT 3.46 (pooled SE=2.19) units more than placebo (IMT mean change=−4.70, SE=1.44, n=14; placebo mean change=−8.16, SE=1.66, n=11). We have used these results on IMT post-HCT to design our study of IMT pre-HCT versus placebo.

Our null hypothesis is there is no difference between the change in days 28±3 days alpha diversity (inverse Simpson’s) post-HCT from baseline in patients receiving pre-HCT IMT compared with patients receiving placebo capsules (ie, the difference in between-arm changes from baseline is zero). Using a two-sample t-test to compare IMT-arm change to placebo-arm change with two-sided alpha controlled at 20%,^20 21^ we need 46 patients randomised 1:1 between IMT and placebo (23 per arm) to have ≥80% power to detect a between-arm difference of 3.46 units (with pooled SD of 5.45 estimated at day 28 post-HCT from mixed-effects model). To account for dropouts at a rate of up to 8% across both arms, we will recruit 50 patients in total. Modelling and sample size calculations have been performed using R V.3.6.1.

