##### Primary estimand

Population: Adults with ALL, AML, AL of ambiguous lineage, high-risk MDS, CMML, and CML in blast phase, considered suitable/fit for allogeneic HCT.

Treatment: Capsulised IMT versus matched capsulised placebo.

Variable: Stool microbiota diversity post-HCT is defined as the change in alpha diversity (measured as inverse Simpson’s index) between IMT administration(at 14±3 days prior to HCT) and 28±3 days after HCT.

Population-level summary: The model-produced estimate for the treatment×time interaction effect at day 28.

Intercurrent events: Death, adverse/serious adverse events (AEs/SAEs), rescue therapy outside of antibiotic use, loss to follow-up/withdrawal.

Strategy to handle intercurrent events: Treatment policy will be used to handle patient all defined intercurrent events, any patient response-assessment data collected postrandomisation will still be used in the analysis model if day 28 data is unavailable.

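### The exploratory responder comparison suggested for the IMT arm alone cannot tell a predictor of IMT effect from regression to the mean or prognosis; use both arms and an interaction

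*Protocol article*

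**What the plan says.** The Discussion of the protocol article first says that "most of our analyses will involve comparison of the dynamics of clinical and biological variables between the IMT and placebo arms". It then adds that "there may also be within-group exploratory analyses which provide further relevant insight as well". The example it gives is a comparison of responders and non-responders "within the treatment arm only, looking for the impact of baseline host gut microbiome diversity and/or specific taxonomic features on the likelihood of response". So the comparison, the candidate predictors and the restriction to one arm are all stated, but the analysis is optional. It does not appear among the estimands or in the analysis sections.

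The article does not say what counts as a response. The variable of the primary estimand is the "change in alpha diversity (measured as inverse Simpson’s index) between IMT administration" and day 28 after transplant, which makes it a natural basis for a responder definition, though the text does not make that link.

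**The concern.** The question behind such an analysis is who benefits from IMT. Answering it needs a contrast between what happens with IMT and what happens without it, at different values of the baseline feature. Inside the IMT arm that contrast is missing, and two other explanations of any association remain open.

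- **Regression to the mean.** If response is a change from baseline, a patient whose baseline happens to be low will tend to show a larger gain or a smaller fall, treated or not.
- **Prognosis.** The Introduction reports that lower diversity before transplant goes with poor survival, and the Discussion repeats the link with morbidity and mortality. A baseline feature that forecasts outcome in everyone will separate good from poor outcomes in the IMT arm too.

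At stake is the reading of an exploratory result: a baseline feature could be reported as marking patients who respond to IMT when it marks nothing specific to IMT.

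**Working it through.** **The plan's own figure.** The article gives no figure for the responder analysis. Its sample size supplies the number per arm used below. Inputs from *Sample size and powering*: difference 3.46, SD 5.45, two-sided alpha 20%, power 80%. Then n per arm = 2 × (1.2816 + 0.8416)² × 5.45² / 3.46² = 2 × 4.508 × 2.481 = 22.4, so 23. The noncentral t gives power 80.3% at 23 per arm and 78.9% at 22. With 8% dropout, 46 / 0.92 = 50. The stated figures reproduce.

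**Response as change.** Let B be baseline, F the day-28 value, r their within-patient correlation and k = SD(F)/SD(B). Then

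corr(B, F − B) = (kr − 1) / √(1 + k² − 2kr),

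which for k = 1 reduces to −√((1 − r)/2). The documents give neither r nor k, so both are assumptions and are shown over a range. For r = 0.5:

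- k = 1: −√0.25 = −0.50
- k = 0.7: (0.35 − 1)/√(1.49 − 0.70) = −0.73
- k = 1.5: (0.75 − 1)/√(3.25 − 1.50) = −0.19

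The sign turns only when kr exceeds 1. For k = 1.5 and r = 0.7 it is (1.05 − 1)/√(3.25 − 2.10) = +0.05.

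**Simulation with no IMT effect.** 20,000 arms of 23 patients; responders are those above the median; baseline diversity is compared by a two-sided 5% t-test. The median split and the t-test are also assumptions. Entries are the share of trials with a false finding in the stated direction, where 2.5% would be nominal.

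| r | corr, k = 1 | change, k = 1: low baseline | change, k = 0.7: low baseline | change, k = 1.5: low baseline | day-28 level: high baseline |
|---|---|---|---|---|---|
| 0 | −0.71 | 86% | not run | not run | 2.5% |
| 0.3 | −0.59 | 66% | 93% | 26% | 19% |
| 0.5 | −0.50 | 48% | 89% | 10% | 48% |
| 0.7 | −0.39 | 30% | 87% | 1.6% | 85% |
| 0.9 | −0.22 | 12% | not run | not run | 99.8% |

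With response defined by an outcome independent of diversity, the rate was about 2.5% in each direction, so there is no artefact.

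**Does the placebo arm remove it?** Change was regressed on baseline, arm and their product, with 23 per arm, no IMT effect and 5,000 runs. The interaction was significant at 5% in 5.3%, 4.8%, 5.3% and 4.7% of runs for r = 0, 0.3, 0.5 and 0.7, which is nominal within simulation error (√(0.05 × 0.95/5,000) = 0.3 percentage points). Using the day-28 level as outcome gives the same interaction estimate, because subtracting baseline only shifts the baseline slope by 1 in both arms.

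**Precision of the interaction.** With equal SDs, the difference between arms in the slope of day-28 value on baseline has a standard error of about √(2/23) × √(1 − r²). At r = 0.5 this is 0.295 × 0.866 = 0.26. For 80% power at two-sided 5% the slopes would have to differ by about 2.80 × 0.26 = 0.7, which is more than the assumed slope of 0.5 itself.

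**The case against.** The strongest reply is that this is a passing example in a Discussion. It is introduced as something that may be done, after a statement that most analyses compare the arms, and full methods are deferred to an SAP that is not shown. That stands, and it sets the priority. Leaving response undefined in an article is also no fault. What remains is that the restriction to the IMT arm is written down, and it is the restriction that causes the problem.

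A reader might infer that low baseline diversity is bound to look predictive. The documents do not support that. Response could be a day-28 level, microbiota engraftment or a clinical outcome, and the direction and size of any bias depend on that choice and on two quantities the article does not give. The planning figures show falls in both groups ("IMT mean change=−4.70, SE=1.44, n=14; placebo mean change=−8.16, SE=1.66, n=11"). Since inverse Simpson's index cannot go below 1, a smaller day-28 variance is plausible, which would enlarge the artefact. This is conjecture, not a stated fact.

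The subtraction argument concerns baseline diversity and does not carry over to taxa in general. For taxa only the wider limit applies: one arm cannot separate prognosis from prediction.

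The 20% level in the article belongs to the primary comparison. No level is given for exploratory work, so 5% is used here.

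**Conclusion.** The point holds as a minor one. For any definition of response related to diversity or to prognosis, a comparison confined to the IMT arm cannot identify predictors of IMT effect. If response is change in inverse Simpson's index, the false-positive rate for low baseline is about 30% to 86% over r from 0.7 to 0, given equal variances, 23 patients, a median split and no IMT effect. It reaches 87% to 93% with k = 0.7, and falls to between 1.6% and 26% with k = 1.5 (both for r from 0.3 to 0.7). With a day-28 level the bias favours high baseline. With a clinical outcome linked to diversity the same direction is expected from the survival association in the Introduction, though this was not simulated.

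Two wider inferences are not supported. The primary and listed secondary comparisons are between randomised arms and are not touched by this. Nor does the article say that the exploratory result would choose patients for a later trial; it speaks only of phase IIa trials in general leading on to phase III.

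**What to change.** If this exploratory analysis is done:

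- State the definition of response before unblinding.
- Use both arms. Model the day-28 level (or the chosen outcome) on arm, the baseline feature and the arm-by-baseline interaction.
- Call a feature a predictor of IMT response only on the strength of the interaction, reported with its confidence interval.
- If a responder split is also shown, apply the same definition to placebo and show the two arms side by side.

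The cost is wording in the SAP and the protocol. The placebo patients' baseline and day-28 diversity are already needed for the primary outcome. The drawback is precision: at about 23 per arm only a large difference in slopes would be detected, so the result will look less striking and should be reported as hypothesis-generating.

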**Figure 2 F2:**
[figure not shown]
‘Prehabilitation’ of the gut microbiome in MAST. Dynamics of the gut microbiota conventionally through the peri-HCT period are shown in black (as defined previously^6^); the red line is our predicted higher starting point and nadir for patients receiving a pre-HCT IMT in the MAST trial. GvHD, graft-versus-host disease; HCT, haematopoietic cell transplantation; IMT, intestinal microbiota transplant; ITU, intensive treatment unit; MAST, Microbiota Transplant Prior to Allogeneic Stem Cell Transplant.

The use of IMT in the context of immunosuppressed patients requires certain considerations above and beyond those of, for instance, conventional use of IMT in treating recurrent CDI.^28^ The use of a capsulised preparation is clearly more acceptable to this patient cohort than conventional IMT slurry and may be safer avoiding potential aspiration of slurry. The donor screening protocol used donors is in full accordance with UK recommendations,^9^ while the risk of CMV transmission via IMT appears extremely low,^29^ CMV negative donors are being used out of an abundance of caution. The window for IMT administration aims to be long enough after prior chemotherapy to allow full cell count recovery, but early enough before HCT to permit sufficient microbiota engraftment. This is important since the degree of microbiota engraftment has been associated with level of clinical improvement after IMT.^30^ Our experience to date is that IMT mitigates the risk of invasive infections related to MDROs rather than decolonises them from the gut,^15^ but there is still uncertainty regarding this; one recent trial of IMT in a renal transplant population suggested certain extended-spectrum beta-lactamases (ESBL)-colonising strains being displaced by non-ESBL strains by strain competition.^31^ The serial clinical assessment and collection of shotgun metagenomic data from study participants in a placebo-controlled fashion will allow a much more granular assessment of the impact of IMT on MDROs than has been described previously.

In conclusion, the MAST trial aspires to give new clinical and translational insights into the role of gut microbiome manipulation in patients with haematological malignancy receiving allogeneic HCT, with particular focus on the potential role of IMT on haematological and infective outcomes. The study aims to run recruitment for 24 months postauthorisation and close in May 2027.

## Ethics and dissemination

### Research ethics approval

The institutional review board (North East—Tyne & Wear South, England, Ref: 23/NE/0105) and the national regulatory authorities, Medicines & Healthcare products Regulatory Agency (MHRA, Ref: CTA 19174/0441/001-0001) issued approval on the 3 October 2023.

#### Other ethical considerations

##### Consent

Patients will be identified as per site-established processes and invited to participate by their primary haematology team. Eligible patients will be provided with the PIS (online supplemental material 2) and given sufficient time to consider the study, with opportunities to discuss and ask questions. Investigators will ensure that they adequately explain the study, including the aims, trial treatment, anticipated benefits and potential risks of participation. The right of the patient to refuse participation in the trial, or withdraw at any point, without giving explanation will be respected. Informed consent will be requested from the patient by the investigator who has been delegated the responsibility on the delegation log. Consent will be obtained no earlier than 24 hours after receiving the PIS to give them time to read and understand what their participation in the study entails (consent form provided as online supplemental material 3). With patient consent, it is the investigator’s responsibility to inform the patient’s general practitioner regarding study participation.

##### Study conduct and safety measures

The study prioritises the highest safety and ethical standards, ensuring full compliance with the 1964 Declaration of Helsinki and ICH GCP E6 guidelines. Rigorous pharmacovigilance measures are in place to monitor and reporting of serious or non-SAEs/reactions to enable a prompt and appropriate clinical response. There are stringent protocols in place for the reporting of causality, expectedness and severity assessments; every reported event undergoes thorough evaluation by clinical professionals. These safety measures are essential for maintaining participant welfare and upholding study integrity. Additionally, robust donor screenings and contraception requirements minimise potential risks associated infection transmission and unanticipated pregnancy outcomes, respectively, to reinforce a comprehensive approach to participant safety.

##### Dissemination

The dissemination of results from this study will always be performed with input from our PPI group. This will be foremost via abstract presentations at conferences and manuscripts in peer-reviewed journals. All such publications will be circulated to all authors prior to submission for their review and approval. Publications will be made in concordance with CONSORT (Consolidated Standards of Reporting Trials) guidelines/checklists. Study participants will be notified of the outcome of the trial prior to any publications. A clinical study report summarising the study results will be prepared and submitted to the research ethics committee within a year of the end of study. The results will also be submitted to the EudraCT results database in accordance with regulatory requirements.
